#### Proposed interim analysis

An interim analysis will be conducted in the middle of the recruitment period to evaluate the effectiveness of the main indexes and to determine whether it is necessary/possible to terminate the trial early.

### Adverse events

#### Definitions

An adverse event is defined as a patient who develops clinical features, such as discomfort or laboratory abnormalities, that are not related to the expected therapeutic effects during central venous catheterisation.

The catheter associated adverse events according to the modified CTCAE V.4 classification^22^ to be recorded are: (1) a broken or cracked catheter; (2) haematoma at the insertion site; (3) chylothorax, pneumothorax, haemothorax or pleural effusion caused by mispuncture or malposition; and (4) arrhythmia or rupture of the atrium caused by malposition, endocarditis because of mechanical stimulation, thrombophlebitis, or injury to the atrium, thoracic duct, brachial plexus or phrenic nerve because of mispuncture.

Severe adverse events (definitely related or possibly related) to be recorded are: (1) death as a result of an adverse event. Medical conditions resulting in death need to be comprehensively reported, such as an underlying disease or an accident; (2) life threatening events. Life threatening events are those events that put the patient at risk of death at the time. This is distinct from an event that may become more serious in the future and put the patient at risk for death; (3) events requiring hospitalisation or that prolong the time of hospitalisation. Hospitalisation in this context means more than one calendar day; and (4) events leading to permanent damage, or medical intervention that must be taken to avoid permanent damage.

An event may meet more than one criterion. If the event could result in harm to a patient or clinician, intervention should be taken to prevent the event, and this adverse event should be recorded as a severe adverse event.

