### Randomisation

Each research centre will receive sequentially numbered containers used to implement the random allocation sequence, and the treatment allocation group will be hidden beyond the coated card. To ensure that patients are randomly assigned at a 1:1 ratio at each study centre, the randomised cards will be protected using a block design (each block includes four random allocation sequences). For a patient who meets the required criteria, the local investigator opens a randomised card that records the screening number and treatment allocation group. Then, the physician in charge of the patient will obtain the correct study catheter and complete catheterisation. Hence treatment allocation will be concealed.

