#### Safety analysis

The proportion of abnormal cases after treatment will be determined, as will the number of cases/incidence of adverse events and severe adverse events. We will also describe the clinical manifestations, degree of all adverse events, and the relationship between these factors and the catheters in detail. Changes in indexes will be described using a crosstab grid. All safety evaluations will be based on the safety set.

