#### Recording and reporting

Researchers must record adverse events and severe adverse events in the corresponding case report form, including signs and symptoms, date, disappearance date (duration), severity or strength, relationship with therapy, measurements and outcomes. If the interim analysis finds that the morbidity of some types of adverse events or severe adverse events and their severity increases significantly, researchers must report the adverse event in a timely manner. All severe adverse events must be reported to the drug administration department and the ethics committee within 24 hours (one working day), and the production enterprise must be informed at the same time.

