#### Follow-up

Researchers must follow-up all adverse events and severe adverse events during the trial. Follow-up will continue until the adverse event or the severe adverse event disappears or becomes stable. All adverse events are to be kept in the case report form until the last observation date.

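### The Definitions section restricts recorded severe adverse events to those judged related, while the sections on recording, reporting and follow-up ask for all of them, so the severe-event incidence may rest on a causality judgement

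*Protocol article*

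**What the plan says.** Four sections of the protocol article bear on which severe adverse events enter the record.

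- **Adverse events, Definitions.** The list of seriousness criteria is introduced by "Severe adverse events (definitely related or possibly related) to be recorded are". The section does not say related to what, or who decides.
- **Adverse events, Recording and reporting.** "Researchers must record adverse events and severe adverse events in the corresponding case report form". The items to be entered include "severity or strength, relationship with therapy, measurements and outcomes". On notification: "All severe adverse events must be reported to the drug administration department and the ethics committee within 24 hours", with one working day given in brackets as the equivalent of that limit.
- **Adverse events, Follow-up.** "Researchers must follow-up all adverse events and severe adverse events during the trial".
- **Safety analysis.** The proportion of abnormal cases will be determined, "as will the number of cases/incidence of adverse events and severe adverse events", and the relationship of events to the catheters will be described.

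On knowledge of the arm, the Randomisation section says that "the local investigator opens a randomised card that records the screening number and treatment allocation group", after which the physician in charge fetches and inserts the allocated catheter.

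**The concern.** Two rules appear to govern the same data. Under the first, a life-threatening event that the site puts down to the underlying illness is not recorded as a severe adverse event. Under the second, it is recorded and its relationship is noted. With 12–16 centres, the same event could be handled in two ways.

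This is a data collection rule, so the harm cannot be repaired later: no analysis plan can restore events that were never entered. Patients in intensive care have many severe events from their underlying disease, so whether an event is possibly related to a catheter is a discretionary call. If that call decides entry and is made by someone who knows which catheter was used, the severe-event counts carry the assessor's opinion as well as the patients' experience. The Recording and reporting section also relies on the interim analysis to notice a rise in the frequency or severity of events, and that check sees only what was entered.

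**Working it through.** **1. The passages side by side**

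| Section | Is relatedness a condition? | Scope |
|---|---|---|
| Definitions, severe-event list | Yes: definite or possible | Events to be recorded |
| Definitions, closing paragraph | No | Events that could harm a patient or clinician are to be recorded as severe |
| Recording and reporting, case report form | No: relationship is a field | Adverse and severe adverse events |
| Recording and reporting, notification | No | All severe adverse events |
| Follow-up | No | All adverse and severe adverse events |
| Safety analysis | No | Number and incidence of both |

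Only the first row has the filter.

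**2. The two readings**

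- *Literal reading.* The later sections mean every severe event. The Definitions list then contradicts them, and a site working from that list omits events the later sections require.
- *Nested reading.* The later sections mean all severe events as already defined. The contradiction goes, but the filter becomes the operative rule. For severe events the relationship field can then hold only definite or possible, and the Safety analysis description of relationship has no unrelated category for them.

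Both readings need a change of text.

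**3. What is exposed**

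Hospital mortality is a secondary endpoint in its own right (Study endpoints) and involves no causality call. The Definitions section also asks for full reporting of conditions that led to death, including underlying disease. That leaves mainly non-fatal severe events. The general definition of an adverse event has no relatedness filter, so some of these could still be entered as ordinary adverse events. That route is uncertain, because the list of adverse events to be recorded is itself confined to catheter-associated ones.

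**4. Hypothetical size**

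The article gives no severe-event figure to reproduce. From the article I take 1818 patients, 10% dropout and 1:1 allocation: 1818 × 0.9 / 2 = 818 per arm. Everything else is assumed: the same true severe-event risk p in both arms, a fraction a₁ or a₂ of events called related, and a two-sided 0.05 test, which the Safety analysis section does not itself specify.

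Recorded rates: r₁ = p·a₁ and r₂ = p·a₂.

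Standard error: SE = √{[r₁(1−r₁) + r₂(1−r₂)] / 818}.

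Chance of a spurious significant difference in the direction of the attribution gap: Φ(|r₁−r₂|/SE − 1.96).

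Example with p = 20%, a₁ = 40%, a₂ = 30%: the recorded rates are 8% and 6%; SE = √[(0.0736 + 0.0564)/818] = 0.0126; 0.02/0.0126 = 1.59; Φ(−0.37) ≈ 0.35.

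| Called related, arm 1 vs arm 2 | p = 10% | p = 20% | p = 30% | p = 40% |
|---|---|---|---|---|
| 30% vs 30% | no induced difference | no induced difference | no induced difference | no induced difference |
| 35% vs 30% | 0.08 | 0.13 | 0.17 | 0.22 |
| 40% vs 30% | 0.20 | 0.35 | 0.51 | 0.65 |

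In the first row the filter creates no false difference, yet 100% − 30% = 70% of severe events go unrecorded as such. The other rows show only that the answer is driven by the assumed gap.

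**The case against.** The strongest reply is that the Definitions section defines the term and the next section uses it, so all severe adverse events means all those just defined. The relationship field still has a purpose: it separates definite from possible, and it serves ordinary adverse events. This reading is tenable. It means one cannot state as fact that sites will drop events the protocol requires. It does not remove the filter.

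Four further replies limit the point:

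- **No between-arm test of severe events is stated.** A reader might infer that the Safety analysis section compares the arms and is open to a spurious p-value. The section says only that numbers and incidence will be determined and events described. The Principles section lists general two-group tests but assigns none to severe events. This objection stands, and the table above is therefore an illustration only.
- **Unmasked causality assessment is an inference.** The Randomisation section shows that the local investigator and the inserting physician see the allocation. No section says that they judge relatedness, and the article does not call the trial open. Equally, it describes no masked assessor.
- **Deaths are largely protected**, for the reasons given in the working.
- **The case report form is not shown.** It may capture every severe event. But the article states both rules itself, so the inconsistency is not just a detail left to a supplement. A form that captures everything would still conflict with the Definitions list.

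**Conclusion.** The point holds in a limited form. The Definitions section makes relatedness a condition for recording a severe adverse event, and the sections that follow do not. If the Definitions rule is followed, non-fatal severe events judged unrelated are not entered as severe events, and the reported incidence depends on a causality judgement probably made by staff who know the arm. That last step rests on the Randomisation section and on the absence of any described masked assessor.

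The loss of events needs only that sites apply the Definitions list. A distortion between arms needs more: attribution must differ by arm, and the article gives nothing from which to estimate that. A reader might take the larger probabilities in the table as the expected bias; they are not, because they follow wholly from an assumed 10-point gap. Neither the primary endpoint nor hospital mortality is touched. The repair is still worth making, because it is cheap and the data cannot be recovered by analysis.

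Separately, and minor: the notification limit is given as 24 hours and, in the same phrase, as one working day. For an event on a Friday evening the first falls due on Saturday and the second on Monday, up to about 72 hours later. This has no bearing on the incidence figures.

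**What to change.** Reconcile the Definitions section with the Recording and reporting and Follow-up sections:

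1. Delete the relatedness condition from the sentence that introduces the severe-event list, so that every event meeting a seriousness criterion is recorded.
2. Keep relatedness as a recorded attribute, with an unrelated category, and state who assigns it and whether that person knows the allocation.
3. In the Safety analysis section, tabulate all severe adverse events by arm, with related events in a secondary table.
4. Check that the case report form and site instructions carry the same rule.
5. Separately, reconcile the two reporting limits so that one remains.

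The cost is a change of wording and more entries at sites that would have followed the Definitions list. On its face, the Recording and reporting section already asks for that work.

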### Patient termination and withdrawal criteria

Participants and their authorised surrogates will participate in the study voluntarily, and therefore they may withdraw from the trial at any time for any reason. Patients may also be withdrawn from the study for: (1) severe adverse events; or (2) violating or deviating from the protocol. If a patient is withdrawn for one of the two reasons mentioned, they should proceed to security analysis.

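### The closing sentence of the severe adverse event definition sets no threshold of harm, so severe event counts and 24-hour reports depend on how each centre reads it

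*Protocol article*

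**What the plan says.** Under Adverse events, the Definitions section of the protocol article gives four alternative routes to severe status for events definitely or possibly related: (1) death; (2) a life threatening event; (3) hospitalisation or its prolongation; (4) permanent damage, or intervention to avoid it. Two of them carry explicit limits:

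- Criterion 2: "Life threatening events are those events that put the patient at risk of death at the time". The text adds: "This is distinct from an event that may become more serious in the future and put the patient at risk for death".
- Criterion 4: "events leading to permanent damage, or medical intervention that must be taken to avoid permanent damage".

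After noting that an event may satisfy several criteria, the section closes with another rule, which begins: "If the event could result in harm to a patient or clinician, intervention should be taken to prevent the event, and this adverse event should". Its consequence is that "this adverse event should be recorded as a severe adverse event".

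The severe label is used in three other places:

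- Safety analysis reports "the number of cases/incidence of adverse events and severe adverse events" on the safety set.
- Recording and reporting requires every severe event to reach the drug administration department and the ethics committee within 24 hours. It also calls for a report if the interim analysis finds a significant increase in some types of adverse or severe adverse event.
- Patient termination and withdrawal criteria names severe events as a possible ground for withdrawal.

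**The concern.** The four criteria describe grave outcomes. The closing sentence asks only whether harm is possible. It gives no degree of harm, no link to any of the four outcomes, and no limit to the patient.

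If centres apply it as written, the boundary between adverse and severe adverse events largely disappears for catheter complications. The two incidences that the safety analysis reports separately would then nearly coincide. If some of the 12–16 centres follow the four criteria and others follow the closing sentence, the severe event rate partly measures how the text was read. The same ambiguity decides which events are expedited within 24 hours and what the interim review sees as a rise in severe events.

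**Working it through.** The plan states no figure on this point, so there is none to reproduce. The check is mainly a comparison of texts.

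**Step 1: what each rule requires.** Criteria (1) and (3) need a death or a hospital stay caused or prolonged. Criterion 2 needs risk of death at the time and sets aside events that might only worsen later. Criterion 4 already contains an intervention clause, but the harm to be avoided must be permanent damage. The closing sentence needs only the possibility of harm of any degree.

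**Step 2: apply the rules to events of the kind on the protocol's own list.** The sentence can be read literally (possible harm is enough) or narrowly (possible harm, and intervention taken to avert it).

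| Event | Criteria (1)–(4) | Closing sentence, literal | Closing sentence, narrow |
|---|---|---|---|
| Small insertion-site haematoma that resolves untreated | none met | severe | not severe |
| Cracked catheter, noticed and replaced without injury | none met | severe | severe |
| Brief arrhythmia that stops when the wire is withdrawn | none met | severe | arguable |

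The literal reading makes all three severe. The narrow reading still captures the cracked catheter, because it keeps the idea of intervention from criterion 4 but drops the threshold of permanent damage. Either reading goes beyond the four criteria, and the two readings disagree on at least one listed complication.

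**Step 3: direction of the effect on counts.** The closing sentence can only add events, so the severe count rises wherever it is applied. The effect on a comparison between arms depends on how the added events are distributed.

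The following is an illustration on assumed rates, none of which is in the document. Let the rates under the four criteria be 4% (ordinary catheter) and 2% (antimicrobial catheter), a ratio of 0.02/0.04 = 0.50. Let a proportion b of the remaining patients in each arm have an event that is severe only under the closing sentence. The recorded rate is then p′ = p + b(1 − p).

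| b, both arms | Ordinary | Antimicrobial | Ratio | Inflation, ordinary arm |
|---|---|---|---|---|
| 0 | 4.0% | 2.0% | 0.50 | 1.0 |
| 5% | 0.04 + 0.05 × 0.96 = 8.8% | 0.02 + 0.05 × 0.98 = 6.9% | 0.78 | 2.2 |
| 10% | 13.6% | 11.8% | 0.87 | 3.4 |
| 20% | 23.2% | 21.6% | 0.93 | 5.8 |
| 30% | 32.8% | 31.4% | 0.96 | 8.2 |

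With equal b the ratio moves towards 1. With unequal b it need not. If b is 5% in the ordinary arm and 10% in the antimicrobial arm, the rates are 8.8% and 0.02 + 0.10 × 0.98 = 11.8%, a ratio of 0.118/0.088 = 1.34. So inflation follows from the rule itself, while dilution rests on an added assumption.

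**The case against.** The case against has several parts.

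- **No contradiction with criterion 2.** A reader might infer that the closing sentence contradicts the exclusion in criterion 2. The text does not support that. The exclusion defines only what counts as life threatening, and an event outside it may qualify by another route. There is tension, but no formal contradiction. This stands.
- **The sentence can be read narrowly**, as covering only events where intervention was needed. That reading is available, but it still has no threshold of harm, and having two readings is itself the difficulty.
- **Hazards to staff.** A reader might infer that a pure staff hazard becomes a patient's severe event. The section defines an adverse event through a patient who develops clinical features, so this is a weak inference. The reference to clinicians is untidy, but little rests on it.
- **No powered comparison is lost.** A reader might infer a measurable loss of power. The safety analysis plans numbers, incidences and description, with no hypothesis on severe events. The general χ²/Fisher rule under Principles could be read to cover them, but the trial was not sized for that. Any power figure would rest wholly on assumed rates. This stands.
- **Withdrawals.** A reader might infer that minor events will remove patients from efficacy follow-up. The text is permissive ("Patients may also be withdrawn from the study for: (1) severe adverse events; or (2) violating or deviating from the protocol"), and nothing says that minor events lead to withdrawal. The route is possible but not shown.
- **The information is kept.** Severity, relationship and outcome are recorded for every event, so a stricter count could probably be rebuilt. This lessens the damage to the tables. It does not make 24-hour reporting consistent between centres.
- **A narrower rule has its own risk.** Under Randomisation the local investigator opens the allocation card, so a judgement of severity may be made knowing the arm. This is a fair warning, and the fix has to meet it.

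**Conclusion.** The concern holds as a fault in a stated definition. The closing sentence has no threshold of harm and no link to criteria (1)–(4). Taken literally, it leaves those criteria largely redundant for catheter complications. The severe event incidence and the 24-hour reports therefore depend on each centre's reading.

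Inflation of severe counts is likely. Dilution of a difference between arms is possible if the added events are similar in both arms. Neither can be sized from the document, which gives no adverse event rates; the figures above show direction only.

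The primary test, its alpha and the sample size are not directly affected. The point deserves correction because safety counts and expedited reporting rest on this sentence and the change is cheap.

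**What to change.** 1. **Definitions.** Reconcile the closing sentence with criteria (1)–(4). An event meeting none of them is recorded as severe only if intervention was needed to prevent one of those outcomes in that patient. Drop the reference to clinicians. This concerns what is recorded as severe, not when staff should intervene.
2. **Case report form.** Record which criterion each severe event meets, with a separate code for events that qualify only under the closing sentence.
3. **Safety analysis.** Tabulate events meeting (1)–(4) separately from any recorded only under the closing sentence.
4. **Events already recorded.** Classify them on the same basis by people who do not know the allocation, since local investigators do.

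The cost is a short text change, one case report form item and a small desk review, with no extra patients or procedures. Fewer events may be expedited, but all remain recorded and graded as adverse events. Coding the criterion and tabulating the two groups separately keeps any reclassification visible and removes most of that drawback.

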#### Recording and reporting

Researchers must record adverse events and severe adverse events in the corresponding case report form, including signs and symptoms, date, disappearance date (duration), severity or strength, relationship with therapy, measurements and outcomes. If the interim analysis finds that the morbidity of some types of adverse events or severe adverse events and their severity increases significantly, researchers must report the adverse event in a timely manner. All severe adverse events must be reported to the drug administration department and the ethics committee within 24 hours (one working day), and the production enterprise must be informed at the same time.

